## Abstract

**Introduction:**

Studies have shown some benefits to single approaches to psychological therapies for the treatment of anxiety in people with intellectual disability such as modified cognitive–behavioural therapy and mindfulness. To our knowledge, no studies have used a multicomponent approach for the individual treatment of anxiety-related disorders in this population group. A co-production group of clinical experts and people with intellectual disability has created a novel multicomponent anxiety management programme (MCAMP-ID). The aims of this study are to investigate (1) the feasibility of this approach in reducing anxiety for people with a mild/moderate intellectual disability, (2) the feasibility of outcome measures and (3) the feasibility of completing a future randomised controlled trial of this programme. The data from this feasibility study will be used to inform trial design and to complete power calculation.

**Methods and analysis:**

Sixty people with intellectual disability will be invited to participate in the study across four intellectual disability services within one mental health trust in Northwest England. The specialist services will deliver either treatment as usual (TAU) or the novel intervention (MCAMP-ID). MCAMP-ID comprises of 10 individual sessions delivered by a member of the clinical team once a week for between 10 and 12 weeks. TAU will be based on standard treatment currently delivered to meet the person’s specific needs. The outcomes of the study will be feasibility of recruitment, attrition, adherence to the programme and suitability of outcome measures. A mixed-methods approach will be used to assess outcomes.

**Ethics and dissemination:**

The study received approval from the Research Ethics Committee and Health Research Authority (23/EM/0044) through the Integrated Research Application System (IRAS ID: 315557) in March 2023. Participants will provide informed consent before taking part. Study findings will be presented at conferences and published within a peer-reviewed journal.

**Trial registration number:**

ISRCTN16062949.

STRENGTHS AND LIMITATIONS OF THIS STUDYFeasibility study to determine if a future definitive trial can be completed.A strength is the use of co-production to develop a manualised multicomponent anxiety management programme.A further strength is the use of a mixed-methods approach, with qualitative and quantitative analyses.A limitation is the anxiety programme manuals have not previously been fully tested in clinical practice, which is the aim of this feasibility trial.

## Introduction

There is a greater incidence of mental health difficulties in people with intellectual disability than in the general population.^1 2^ Anxiety-related issues are the most common^3 4^ Some evidence suggests anxiety difficulties may increase over a person’s life course due to exposure to negative life events which can impact on quality of life.^5 6^ High levels of anxiety in people with intellectual disability is sometimes demonstrated as behaviour of challenge, for example, self-injury, aggression or property damage, since individuals may be unable to effectively communicate or cope with high levels of stress and anxiety.^7^ Subsequently, there can be a tendency for interventions to focus more towards behavioural management strategies.^8^

Anxiety can have a significant effect on quality of life and limit opportunities to engage in social and recreational activities. This can result in people experiencing poor self-esteem, low mood, increased isolation, loneliness and cognitive distortions.^3^ Equally, people with intellectual disability can have difficulty making sense of their own thoughts, with overcoming avoidance behaviours or developing effective self-management strategies.^9^ Psychoeducation is an important component in treatment for anxiety-related difficulties for people with intellectual disability because it helps the individual to understand that they can influence their illness experience and live a better quality of life.^10^ Therefore, the efficacy of psychological therapies is of paramount importance given the prevalence of mental health difficulties in this population group.^11^

In the UK, clinical guidance for the treatment of mental health difficulties in people with intellectual disability highlighted the limited body of evidence for effective psychological therapies^12^ (National Institute for Health and Care Excellence (NICE)). However, there are a small but growing number of studies which have examined the effectiveness of adapted psychological therapies for the treatment of mental health problems.^13^

Studies have examined modified cognitive–behavioural therapy (CBT) for a range of emotional problems for people with intellectual disability.^14^ A feasibility randomised controlled trial (RCT) of CBT for the treatment of depression and anxiety in people with a mild intellectual disability demonstrated limited long-term effectiveness.^15^ A meta-analysis examining CBT for the treatment of a range of mental health problems found limited efficacy for the treatment of anxiety in people with intellectual disability.^13^ More significant and sustained improvements in anxiety and depression symptoms were reported for 12 people with intellectual disability in a study examining a modified transdiagnostic programme of CBT.^16^ Discrepancies may be partly explained by a systematic review finding small sample sizes and lack of methodological rigour in study designs a significant factor in identifying clinical effectiveness within study outcomes.^17^

Studies of psychological therapies such as mindfulness have been found to be effective when people with intellectual disability are provided with adequate support and guidance to practise requisite skills.^13 18 19^ NICE clinical guidelines suggest psychological therapy be adapted for people with intellectual disabilities, identifying CBT, relaxation and graded exposure techniques as recommended treatment for anxiety.^12^ However, despite recommendation, there is no current evidence of any adapted multicomponent therapies for the treatment of anxiety in people with intellectual disability.

Multicomponent therapies combine key therapeutic skills that work together to improve the effectiveness of treatment.^20^ More recently, some success of multicomponent therapies for anxiety in the general adult population has been identified which demonstrates promise for this psychological approach.^21^ There are very few adapted therapies for mental health difficulties that are suitable for people with a moderate intellectual disability as well as those with a milder intellectual impairment.^19 22^

### Co-producing a multicomponent anxiety management programme manual

We have worked with people with intellectual disability with a lived experience of mental health difficulties to co-produce and develop a multicomponent psychological therapy for the treatment of anxiety. A five-phase process (Box 1) was used to guide the adaptation of psychological therapies included within the treatment manuals.^23^

Box 1Five-phase process for adapting psychological therapiesPhase 1: generating knowledge and collaborating with stakeholders.Phase 2: integrating generated information with theory and empirical and clinical knowledge.Phase 3: review of culturally adapted clinical intervention by stakeholders and further revision.Phase 4: testing the culturally adapted intervention.Phase 5: synthesising stakeholder feedback and finalising the culturally adapted intervention.

An initial draft clinician and service user’s manual was subsequently developed with input from specialist clinical staff, service users, their families and carers.^24^ Initial trialling of sessions with people with intellectual disability was completed and feedback allowed modifications to the programme including increasing the number of treatment sessions to 10.

### Aim and objectives

The aim of this study is to discover the feasibility of this approach in reducing anxiety for people with mild or moderate intellectual disability. Additionally, we will establish the feasibility of conducting a future RCT using a multicomponent approach for the treatment of anxiety and development of self-management skills in people with intellectual disability. This will be assessed by examining recruitment, attrition rates, adherence to the treatment programme and National Health Service (NHS) treatment costs.

Our secondary objective is to assess the appropriateness of outcome measures which include the Glasgow Anxiety Scale (GAS-ID),^25^ Hospital Anxiety and Depression Scale (HADS),^26^ adapted WHO Quality of Life (WHOQOL-8)^27^ and Client Satisfaction Questionnaire (CSQ-8)^28^ with the intervention. We will complete power calculation to estimate sample size for future RCT.

## Methods and analysis

### Study design

This feasibility study is a randomised controlled quasi-experimental trial of a novel multicomponent anxiety management intervention in comparison with treatment as usual (TAU). Each arm of the study will have 30 participants and they will be allocated between four sites, with two sites comprising the control group and the other two sites the intervention arm. To reduce selection bias, group allocation will be completed by allocating each team with a number and one investigator placing numbers in an envelope and an independent person randomly selecting numbers for the assignment of groups.

The intervention will be delivered over the duration of 10 weeks to allow for some flexibility to meet the needs of people with severe intellectual disability. Baseline measures will be completed 1 week prior to the intervention, at the end of the intervention (12 weeks) and again at follow-up 8 weeks post-completion to establish any sustained effect on levels of anxiety.

The feasibility trial will be supported by people with intellectual disability who have a lived experience of mental health issues and will form an essential part of the patient and public involvement (PPI) group.

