### Sample size

A total of 60 adults with intellectual disabilities will be invited to participate in the study. Sample sizes of between 50 and 60 are considered large enough to allow sufficient power to evaluate feasibility of a definitive RCT.^30^

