### Quantitative analysis

Data will be analysed using the computer software program SPSS (V.28). The descriptive analysis will focus principally on recruitment rates, characteristics of participants and the function of the programme manuals. The primary outcomes (mean scores and CIs) will be reported at baseline, 12 weeks and 20 weeks (8 weeks post-completion) for both comparative arms. The variability of the primary outcome measure will be used to inform the power calculation and sample size for the definitive RCT. Additionally, we will complete analyses of treatment preference and number of sessions received.

A descriptive analysis of total NHS costs and individual resource use components will be completed.

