### Criteria for progression to full RCT

We will consider progressing to a full RCT, if we are able to recruit and retain participants. Therefore, feasibility of recruitment will be a key aspect of this feasibility study. A Stop/Go process will be used to ascertain the percentage of participants recruited to the trial. Go: 100% recruited and at least 80% of eligible participants retained. Review: 50–79% of eligible participants recruited; Stop: <50% participants recruited. With the retention rate of 80%, a sample size of 60 will allow these outcomes to be estimated with an accuracy of ±11%.

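### Treatment is allocated by team, two sites per arm, but the sample size, the arm CIs and the ±11% precision take no account of site

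*Protocol article*

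**What the plan says.** **Allocation.** Under Study design, "group allocation will be completed by allocating each team with a number and one investigator placing numbers in an envelope", from which an independent person draws. The result is that participants are spread over sites and "they will be allocated between four sites, with two sites comprising the control group and the other two sites the intervention arm". The same section says "Each arm of the study will have 30 participants".

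**Sample size.** "A total of 60 adults with intellectual disabilities will be invited to participate in the study", justified by a rule of thumb: "Sample sizes of between 50 and 60 are considered large enough to allow sufficient power to evaluate feasibility of a definitive RCT". The rule is stated in people. The number of sites does not enter.

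**Analysis.** Under Quantitative analysis, "The primary outcomes (mean scores and CIs) will be reported at baseline, 12 weeks and 20 weeks (8 weeks post-completion"), for each arm. Then: "The variability of the primary outcome measure will be used to inform the power calculation and sample size for the definitive RCT".

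**Precision.** Under Criteria for progression to full RCT: "With the retention rate of 80%, a sample size of 60 will allow these outcomes to be estimated with an accuracy of ±11" per cent. This is the only computed figure in the article.

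Site, clustering, ICC and design effect appear in none of the sample size, analysis or progression text.

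**The concern.** When whole teams are allocated, people at the same site share clinicians, local practice and referral patterns, so their outcomes tend to be alike. Sixty people in four sites then carry less information than 60 independent people, and any interval that treats them as independent is too narrow.

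Two uses of the results are exposed. First, retention near 80% is a progression threshold, and the ±11% tells the reader how well it will be known. Second, the article's aim includes feasibility in reducing anxiety, and the 20-week assessment is meant to show whether an effect lasts. Readers will therefore set the two arms' GAS-ID intervals side by side, although a difference between them may simply be a difference between sites.

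**Working it through.** **Inputs.** Four sites, two per arm, 30 per arm (Study design); N = 60 (Sample size); retention 80%, ±11% (Criteria for progression). Assumed: equal site size, m = 30/2 = 15, and ICC 0.02 / 0.05 / 0.10, because the article gives no ICC. The ICC for retention may differ from that for GAS-ID; the same range is used for both.

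**1. The plan's own figure.** 95% half-width for p = 0.80, n = 60, people independent:
- Wald: 1.96 × √(0.8 × 0.2 / 60) = 10.12 points
- with continuity correction, adding 1/(2 × 60) = 0.83: 10.95 points
- exact for 48/60: 67.7% to 89.2%, half-width 10.8 points

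The last two round to 11, so the figure reproduces with no clustering term.

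**2. Design effect.** DE = 1 + (m − 1) × ICC; effective N = 60/DE; Wald half-width for retention = 10.12 × √DE.

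| ICC | DE | √DE | Effective N | Retention half-width (points) |
|---|---|---|---|---|
| 0 | 1.00 | 1.000 | 60 | 10.1 |
| 0.02 | 1 + 14 × 0.02 = 1.28 | 1.131 | 47 | 11.45 |
| 0.05 | 1 + 14 × 0.05 = 1.70 | 1.304 | 35 | 13.2 |
| 0.10 | 1 + 14 × 0.10 = 2.40 | 1.549 | 25 | 15.7 |

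**3. Coverage of an arm-mean CI that ignores site.** Approximately 2Φ(1.96/√DE) − 1 = 91.7 / 86.7 / 79.4%. Simulation (20,000 trials, two sites of 15 per arm, t interval on 29 df) gave 91.8 / 86.7 / 79.0%.

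**4. Between-arm difference in GAS-ID, in SD units.** Ignoring site: t(58 df) × √(2/30) = 2.00 × 0.258 = 0.52. Respecting site, with 4 − 2 = 2 df: t(2 df) × √(2 × DE/30) = 4.303 × 0.258 = 1.11 at ICC 0, and 1.11 × 1.304 = 1.45 at ICC 0.05. Even with no clustering at all, the honest interval is about twice as wide.

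**5. Does ignoring site distort the SD?** The expected within-arm variance, as a share of total variance, is (1 − ICC) + ICC × 15/29. At ICC 0.10 this is 0.90 + 0.052 = 0.952, an SD ratio of 0.976. At ICC 0.02 and 0.05 the ratios are 0.995 and 0.988. The SD moves by about 2.5% at most.

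**6. Can four sites supply an ICC?** No. In simulation at true ICC 0.05, 95% of the estimates lay between −0.07 and 0.29, and 43% were zero or below.

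**The case against.** The best defence is that this is a feasibility study. It plans means and CIs, no p-value, and its progression rule rests on recruitment and retention. Team allocation is disclosed, and the study calls itself quasi-experimental. The CI formula is not stated and may sit in an analysis plan that is not shown. All of this stands, and it lowers the severity. It does not rescue the ±11%, which the article itself states and which matches independence. That match is strong evidence but not proof: a Wald interval with ICC 0.01 gives 10.12 × √1.14 = 10.8, which also rounds to 11, although the article mentions no such factor.

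Several stronger readings are tempting and are not supported:
- **The SD for the definitive trial is fragile because site is ignored.** Step 5 shows it is barely affected. Its uncertainty comes from the small N (95% limits 0.85 to 1.22 times the estimate on 58 df) and would be the same in any study of this size. The article says only that the variability will inform the calculation, not that a raw point estimate will be used.
- **The type I error is inflated, or the smallest attainable p is 2/6 = 0.33.** Both describe a test that the article does not plan.
- **Arm is fully confounded with site.** Two sites per arm leave 2 df. That is very weak, but it is not full confounding.
- **Recruitment here misjudges recruitment to the RCT.** That depends on whether the RCT will randomise individuals, which the article does not say.

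**Conclusion.** The unit of allocation is the team, while the sample size rationale and the stated precision are built on individuals, and the arm CIs are described without reference to site. For any positive ICC, intervals computed on independent participants are too narrow: by a factor of 1.13 to 1.55 in half-width over ICC 0.02 to 0.10, with the coverage losses in step 3. The retention margin becomes roughly 11 to 16 points on the Wald scale, against 10.1 without clustering. No between-arm conclusion on anxiety can be supported with 2 df.

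These sizes rest on the assumed ICC range and equal site sizes; their direction does not. Severity is moderate, because the plan is descriptive and the error lies in how precision is stated rather than in a planned test.

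**What to change.** 1. Describe the study as site- (cluster-) allocated, with four clusters.
2. Report recruitment, retention and GAS-ID n, mean and SD by site within arm.
3. Label the arm CIs as descriptive and not adjusted for site, and state that no between-arm conclusion will be drawn. Recomputing them with site as the unit is no remedy: with two sites (1 df, t = 12.7) the half-width is 2.3 SD even at ICC 0.
4. Restate the ±11% over a range of design effects, with the assumed ICCs shown.
5. Say which unit the definitive trial will randomise. If sites, apply an ICC range from outside this study to the total SD. Applying a design effect to a within-site SD would understate N by the factor (1 − ICC), that is by 2 to 10% over this range. If individuals, state that recruitment here does not show willingness to be individually randomised.

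Optional, and prompted by the small N rather than by site allocation: size the definitive trial on an upper confidence limit for the SD, and report the correlation of GAS-ID between baseline and follow-up.

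The cost is some wording, a few more table rows and wider stated precision. Conduct of the study does not change.

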### Study timeline

The study will be completed over 24 months that started on 29 March 2023. Recruitment started on 3 March 2023 and will continue until August 2024. Follow-up assessments, data cleansing and analysis will be completed between September 2024 until March 2025.

### Recruitment and screening

Participants will be recruited from four community intellectual disability services within the Northwest region of England. Participants will be identified from people currently requiring treatment or those referred to specialist intellectual disability services for an anxiety-related difficulty.

Professionals from intellectual disability services will be provided with information on inclusion/exclusion criteria and asked to screen their caseloads to identify potential participants. Participants will be provided with accessible information about the study and given the opportunity to meet a member of the research study team, if they require further information.

Potential participants who are interested in taking part will be asked permission for their name and contact details to be provided to the research study team. A member of the team will contact the person and their family or carer and arrange a visit to assess if they meet the inclusion criteria. If the person meets the eligibility criteria and is willing to participate, then informed consent will be obtained.

Participants will be screened for eligibility using the anxiety component of the Moss-PAS-ID anxiety.^29^ Participants will be eligible for the study if they score 7 or above.

### Sample size

A total of 60 adults with intellectual disabilities will be invited to participate in the study. Sample sizes of between 50 and 60 are considered large enough to allow sufficient power to evaluate feasibility of a definitive RCT.^30^

### Inclusion criteria

Participants aged over 18 years of age.Registered diagnosis of mild or moderate intellectual disability with or without autism.Scores above 7 (range 7–18) on the anxiety component of the Moss-PAS-ID. 29Required to provide informed consent and sign a declaration form indicating agreement to participate.

### Exclusion criteria

If they choose not to be involved in the study.Have a severe or profound intellectual disability.Lack capacity to consent.Under the age of 18 years old.Participants who score below 7 on the anxiety component of the Moss-PAS-ID.

All decisions regarding participant exclusion will be made by the specialist intellectual disability clinical team.

### Capacity and consent

All participants will be required to have capacity to consent to taking part in the study. This will be assessed, if required, by a member of the research team in line with Mental Capacity Act (2005). Participants will be provided with information about the study in an accessible format and provided with an opportunity to discuss or find out more about the study prior to agreeing to participate.

Participants who agree to participate will be asked to sign a consent form to indicate their agreement to be part of the trial (online supplemental material). If at any time a participant decides they no longer wish to take part in the study, they will be made aware of their right to withdraw by notifying a member of the research team.

10.1136/bmjopen-2023-078411.supp1Supplementary data

### Intervention group

The novel multicomponent anxiety management programme (MCAMP-ID) intervention will comprise of up to 12 face-to-face sessions using a co-developed novel anxiety management manual for the delivery of treatment sessions. Each session begins and ends with a breathing exercise to support skill learning before the main anxiety management activity session. The first session provides an outline of the programme, selects a location for sessions and establishes ground rules before introducing anxiety and developing a person-centred plan and therapy goals. Table 1 provides an overview of session structure.

**Table 1 T1:** Overview of session structure

Session no	Session plan	Session summary
1	Introduction	Basic introduction to anxiety, setting out the components of the therapy, and practical considerations, goal setting.
2	Healthy mind and body	Simple healthy living principles that provide a foundation to cope with anxiety, for example, diet, exercise and sleep factors.
3	Talking about anxiety	Further psychoeducation about anxiety, for example, anxiety is a normal emotion, physiology and language to describe anxiety.
4	Learning new skills	Practical introduction to mindfulness and self-soothing skills.
5	Working on my anxiety skills	Considering potentially anxiety-producing scenarios (scenario cards) and coping skills that could support.
6	One step at a time	Revisiting personal goals, developing a graded exposure plan and using anxiety skills to facilitate steps.
7	My second step	Review of progress so far, troubleshooting, further practise of anxiety-coping skills, setting next steps towards goals.
8	My third step	Review of progress since the prior session so far, troubleshooting, further practise of anxiety coping skills, setting next steps towards goals.
9	My last step	Review of progress since the prior session and next steps to continue progress after the programme.
10	My anxiety plan	Developing personalised plan to include consolidation of all aspects of the programme including goals, lifestyle factors, anxiety management skills and mindfulness and soothing skills. Provision of separate summary for supporters to help the person continue their progress.

